### 7.2.2. Drop-outs

If the primary outcome variable and the primary explanatory variable are missing, the patient will be censored from the analysis. Adjusting variables will be imputed with regression-based imputation.

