#### *Follow-up of recipients*

Recipient baseline data, including demographics and medical history, is recorded at inclusion. The recipients will be followed regarding death, need of mechanical heart pump and re-transplantation during the first year (primary outcome variable). Short-term data will be collected regarding need of post-operative mechanical assistance, intra-aortic balloon pump, dialysis, time with mechanical ventilation, inotropic drugs, re-surgery(s), time at the ICU, time at the home clinic/other department, time before returning home. The recipients will be followed according to clinical routine at the participating center, and no extra examinations are planned, with the exception that echocardiography is preferable performed at  $24 \pm 6$  hours for assessment of PGD.

The active follow-up end at one year after transplantation. Long-term complications that will be followed are death, need for mechanical heart pump, re-transplantation, rejection/coronary vasculitis, other organ failure. To investigate whether recipients of hearts with dysfunction have increased risk for other disease, data will be collected from the Swedish National Board of Health and Welfare's (Socialstyrelsen) Patient Register and Cause of Death Register. Those data that will be requested are all of the patients' ICD codes and medical procedure codes at 1, 3, 5, and 10 years after transplantation. Data may be collected from other national registers if they are available.

A list of variables is available in *Attachment 2*.

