## 7.4. Sample size calculations

This is a non-inferiority trial. Power calculations are made based on non-inferiority calculations. Based on our retrospective data, the absence of death/retransplantation within a year was 90%. We have calculated power to exclude a difference in the primary outcome of 10%, which is the benefit that may be relevant since patients can be transplanted earlier and more patients can be transplanted. We expect that 20% of the transplantations will come from hearts with dysfunction. The power calculation says then that we need 445 transplanted hearts and at least 89 transplanted hearts with dysfunction. Since we do not know the exact incidence, outcome, or transplantation frequency of hearts with dysfunction in a prospective cohort, we primarily plan to include 500 heart-transplanted patients in the study.

To be able to answer our specific research questions about the heart donors, we estimate that we need at least 100 donors of hearts with dysfunction to be able to have a representative group. With an estimated incidence of cardiac dysfunction in 25% of the donors, at least 400 possible heart donors are needed in the study. However, the study intends to continue collecting data from all donors until the primary objective is answered.

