### 9.3. Procedure for obtaining informed consent

Heart recipients will be asked about inclusion in the study during the time window from when he/she is accepted for transplantation until he/she is transplanted. In the first place, inclusion will be requested in connection with the visit in which the patient is accepted for transplantation. The physician who is responsible for the transplant investigation or study personnel, well initiated in the study, will ask about inclusion. Oral and written information will be provided. The patient will also be given the opportunity to ask questions. The patient can go home and provide a response about study participation later. Consent is documented in writing.

The principal investigator at each site shall ensure that the subject is given full and adequate oral and written information about the study, its purpose, any risks and benefits as well as inclusion and exclusion criteria. Research subjects must also be informed that they are free to discontinue their participation in the study at any time without having to provide a reason. Research subjects should be given the opportunity to ask questions and be allowed time to consider the provided information. If the person chooses to participate, both the research subject and the investigator shall sign the informed consent form. A copy of the subject information form as well as the informed consent form shall be provided to the research subject. The research subject's signed and dated informed consent must be obtained before performing any study-specific activity in the study. Each research subject who participates in the study will be identified by a subject number on a subject identification list. The research subject agrees that monitors and inspectors may have access to their medical records. If new information is added to the study, the research subject has the right to reconsider whether he/she will continue their participation.

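### The drop-out rule in section 7.2.2 is misworded and in effect deletes patients without a one-year outcome, while the 1-year register extract already planned in section 4.1 is not used to complete that outcome

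*Protocol*

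**What the plan says.** Section 7.2.2 (Drop-outs) has one rule for the main variables: "If the primary outcome variable and the primary explanatory variable are missing, the patient will be censored from the analysis". Its only other sentence says that missing adjusting variables are filled in by a regression-based method. The outcome is not.

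Section 7.2.1 analyses the primary outcome by binary logistic regression. The outcome is a composite of death, retransplantation or long-term mechanical assistance within one year, and the explanatory variable is donor heart dysfunction.

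Section 4.1 (Follow-up of recipients) plans to request data from the Swedish Patient Register and Cause of Death Register, namely all "ICD codes and medical procedure codes at 1, 3, 5, and 10 years after transplantation". The stated purpose is to study the risk of other disease. Other national registers may be used if available. No section names any of these as a source for the primary outcome.

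Section 7.4 states "This is a non-inferiority trial" and concludes that "we need 445 transplanted hearts and at least 89 transplanted hearts with dysfunction". It gives no expected loss to follow-up.

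**The concern.** The rule has two faults of wording. First, *and* requires both variables to be missing. A recipient who leaves follow-up has a known donor heart and an unknown outcome, so a section on drop-outs leaves out the typical drop-out. Second, a binary logistic regression has no censoring: a patient either has a one-year outcome and enters the model, or has none and does not. Whatever was meant, the effect is a complete-case analysis.

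Complete-case analysis assumes that, given donor function and the adjusters, patients without an outcome fare like those with one. In a non-inferiority comparison with a small index group, unrecorded events in that group pull the estimate towards the conclusion the study hopes to reach. Part of this risk is avoidable, because a 1-year extract that should show deaths and relevant procedures is already planned.

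**Working it through.** **Inputs from section 7.4.** Event-free proportion 90% at one year, so 10% events; margin 10 percentage points; 20% of transplants from impaired hearts, so 1:4; 445 patients in total and 89 impaired, hence 445 − 89 = 356 normal. **Assumed:** one-sided 0.025 and 80% power (neither is stated), and an unadjusted risk difference with a two-sided 95% Wald interval (the protocol does not say how the logistic model is to be set against the margin).

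**Step 1: the plan's own figure.** With unpooled variance, the number of normal hearts is (0.9 × 0.1 + 0.9 × 0.1 / 0.25) × (1.960 + 0.842)² / 0.10² = 0.45 × 7.849 / 0.01 = 353.2. The impaired number is 353.2 / 4 = 88.3, rounded up to 89, and 89 × 5 = 445. The stated size is reproduced exactly, with no allowance for missing outcomes. Section 7.4 does plan for 500, but because incidence, outcome and transplantation frequency are uncertain. Section 4.4 ends the study on patients included, not on outcomes known.

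**Step 2: no loss.** Upper limit = p1 − p0 + 1.96 × √[p1(1 − p1)/n1 + p0(1 − p0)/n0]. For 9/89 v 36/356 both risks are 10.1%, the standard error is 3.57 points and the upper limit is 0.0 + 1.96 × 3.57 = 7.0 points.

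**Step 3: worst-case bound, loss in the impaired group only.** Three impaired-heart patients have no recorded outcome, all three had events, and no normal-heart patient is lost.

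| Analysis | Impaired | Normal | Difference | Upper limit | Within 10 points? |
|---|---|---|---|---|---|
| Three deleted | 9/86 = 10.5% | 36/356 = 10.1% | 0.4 | 7.5 | yes |
| Three counted as events | 12/89 = 13.5% | 36/356 = 10.1% | 3.4 | 11.1 | no |

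Three is the smallest number that reverses the Wald result: with two, 11/89 gives 9.8. By the Newcombe interval two suffice (9/87 gives 8.8, 11/89 gives 11.1). At the planned 500 (100 v 400), three again suffice by Wald: 10/97 gives 7.0 and 13/100 v 40/400 gives 10.2.

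**Step 4: the same loss in both groups.** Suppose 4 of 89 and 16 of 356 (4.5% each) are lost and all had events. The full data are then 13/89 v 52/356, both 14.6%. The standard error is 4.19 points and the upper limit 8.2, so non-inferiority still holds.

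**Step 5: loss unrelated to outcome.** Power falls from 80.3% with no loss to 79.5%, 78.3% and 76.1% at 2%, 5% and 10% loss. The issue is bias from differential loss, much more than power.

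**The case against.** The strongest case on the other side is that the numerical harm needs an unlikely pattern: losses confined to impaired-heart recipients, all of whom had events. No section gives a loss rate or suggests differential loss. Recipients are followed in clinical routine at transplant centres, with mortality checks at 3 and 6 months and data collection at one year. Deaths, retransplantations and device implants are hard to miss there. Section 4.1 also does not forbid using the register for the primary outcome. All of this stands, and it makes Step 3 a bound and not a forecast. It does not repair the wording, and it does not explain why an extract already requested has no stated role for the outcome that matters most.

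Four stronger readings are tempting but not supported:

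- **That a few losses will decide the trial.** Step 4 shows that equal proportional loss does not reverse the result.
- **That deletion discards known event-free time.** The 3- and 6-month checks in section 4.2 record mortality only, so a patient alive at 6 months is not known to be free of retransplantation or mechanical assist.
- **That the registers would recover every outcome.** The two named are Swedish. Section 7.2.1 counts only long-term assistance, which procedure codes may not identify. Section 3.4 lists register outcomes at 3, 5 and 10 years, so the 1-year extract rests on section 4.1 alone.
- **That section 9.3 needs a change on withdrawal.** The right to discontinue is standard, and the consent pages are not available, so how register permission is handled cannot be judged.

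Nor is the absence of multiple imputation a fault. That detail commonly sits in an SAP, and imputing under missing-at-random would not turn lost patients into events in Step 3.

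**Conclusion.** The point holds as a defect of wording with an avoidable risk of bias. Two things are certain from the text: the rule misses the ordinary drop-out, and it uses a term that has no meaning in the stated model. That its effect is complete-case deletion follows from the choice of logistic regression. That the planned 1-year extract is not assigned to the primary outcome also follows from the text.

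The size is a worst case only: three event-bearing losses among 89 impaired-heart recipients, with none among normal hearts, move the upper limit from 7.5 to 11.1 points against a margin of 10. This rests on 10% events, an unadjusted Wald interval and wholly one-sided loss. The adjusted analysis could differ, and actual loss may be small. The correction is worth making before the final analysis because it is cheap and removes most of the doubt.

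**What to change.** In section 7.2.2:

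1. Replace *and* with *or*, and *censored* with *excluded*.
2. State that, before any patient is excluded, death, retransplantation and, where procedure codes allow, long-term mechanical assistance at one year will be completed from the 1-year register extract planned in section 4.1, or from other national registers where available, by the same procedure in both groups.
3. For outcomes still missing, report a sensitivity analysis that varies the assumed event rate separately in each group and shows where the conclusion changes against the 10-point margin.

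In section 4.1, add completion of the primary outcome to the stated purpose of the extract.

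The cost is a few sentences and one further analysis. The final analysis may have to wait for the extract. Coverage will stay incomplete for patients outside Sweden and for the mechanical-assist component, and step 3 is there for those gaps.

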## 7.3. Adjustment of significance and confidence interval

In cases where multiple significance (multiplicity) can occur, data will be adjusted with Bonferroni Holm.

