#### 3.2. Secondary objectives

The secondary research questions that this study intends to answer are the following:

Does cardiac function differ postoperatively in a recipient who has received a donor heart with a functional impairment compared to a recipient who has received a donor heart with normal function?

With a systematic consideration of hearts with impaired function, by how much do the number of heart transplantations increase and how much faster can a patient be transplanted?

Does cardiac function in the donor affect cardiovascular events over time in the heart-transplanted patients?

Using cardiac biomarkers, ECG, echocardiographic imaging, and clinical data, can it be predicted early on which hearts will improve/recover function during the donation process?

Using cardiac biomarkers, ECG, echocardiographic imaging, and clinical data, can cardiac dysfunction caused by primary heart disease be ruled out?

Do donor hearts with dysfunction have different histology and/or biochemistry?

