### 3.4. Secondary variable

The secondary variable is: frequency of left-sided moderate or severe primary graft dysfunction (PGD).

Moderate PGD is defined as having *at least one of the following at 24 hours after cross-clamp release*:

- Ejection fraction  $\leq 40\%$ , *or* hemodynamic compromise with right atrial pressure (RAP)  $> 15\text{mmHg}$ , pulmonary capillary wedge pressure  $> 20\text{mmHg}$ , cardiac index  $< 2.0$ , hypotension with a mean arterial pressure  $< 70\text{mmHg}$   
*And at least one of the following:*
- High-dose inotropes (Inotrope score  $> 10$ ) *or* newly placed intra-aortic balloon pump.

Severe PGD is defined as dependence on left or biventricular mechanical support in the form of either ECMO, LVAD, BiVAD, or percutaneous LVAD at 24 hours after cross-clamp release.

The following outcome variables apply to the secondary research questions:

Need for interventions and complications in the postoperative course including, for example, mechanical heart pump, intra-aortic balloon pump, need for mechanical ventilation, need for dialysis, dose and time with inotropic and vasoactive medications.

Occurrence of ICD codes for cardiovascular disease in the Patient and Cause of Death registries for participating patients at 3, 5, and 10 years after transplantation.

Levels of cardiac biomarkers, occurrence of specific echocardiographic changes, ECG changes, and clinical data in donors with recovered and non-recovered cardiac function during the donation process, respectively.

Levels of cardiac biomarkers, occurrence of specific echocardiographic changes, ECG changes, and clinical data in donors with primary and non-primary heart disease, respectively.

Estimation of the number of extra patients who would be able to receive a heart transplantation with a systematic utilization of donor hearts with dysfunction.

Presence of specific histological changes and specific proteins in heart tissue with dysfunction and normal function, respectively.

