#### 4.3.1. Handling, storage, and destruction of biological samples

The hearts of organ donors that are not transplanted may be used for tissue analysis, when logistically feasible and permission is granted, in accordance with national regulations. The hearts will be examined for coronary heart disease and myocardial infarction. Tissue samples will be taken from several areas with affected (in such donors) and normal function. Histological analyses, Western blot, and analyses for proteomics are planned. The analyses are planned to be performed at Wallenberg lab as well as the Core facilities at Sahlgrenska Academy.

Blood samples from donors will be taken when logistically feasible and permission is granted, in accordance with current regulations. Blood samples are planned to be analyzed by enzyme-linked immunosorbent assay (ELISA). The analyses are planned to be performed at Wallenberg lab and Lab of immunology, Sahlgrenska Academy.

Samples will be saved up to 10 years after the study has ended.

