## 7.2. Statistical analyses

### 7.2.1. Statistical methods

The primary variables will be analyzed with binary logistic regression. The primary outcome variable will be incidence of death, re-transplantation or need of long-term mechanical assistance within one year after transplantation. The primary explanatory variable is incidence of cardiac dysfunction in the donor, defined as regional hypokinesia and/or ejection fraction < 50%. The analysis will be adjusted for age of recipient, age of donor, need of mechanical assistance before transplantation and "urgent call" status of transplantation.

For statistical significance, the p-value must be  $> 0.05$ .

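### The unqualified Bonferroni-Holm rule in section 7.3 also reaches the exploratory tissue proteomics, where a false-discovery-rate rule suits the question better and may recover much power

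*Protocol*

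**What the plan says.** The whole of Protocol section 7.3 is: "In cases where multiple significance (multiplicity) can occur, data will be adjusted with Bonferroni Holm". No family, tier or exception is named there or elsewhere in section 7, and no false-discovery-rate method is mentioned.

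The tissue work is set out in three places:

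- Section 3.2 lists as a secondary question: "Do donor hearts with dysfunction have different histology and/or biochemistry".
- Section 3.4 gives the matching outcome variable: "Presence of specific histological changes and specific proteins in heart tissue with dysfunction and normal function, respectively".
- Section 4.3.1 states: "Histological analyses, Western blot, and analyses for proteomics are planned". It limits the source of tissue: "The hearts of organ donors that are not transplanted may be used for tissue analysis, when logistically feasible and permission is granted". It also says that samples come from several areas of the heart.

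The protocol does not state the proteomic platform, the number of proteins, the number of hearts with tissue, the expected difference or its variability. Section 7.4 says of the donor questions that "we estimate that we need at least 100 donors of hearts with dysfunction to be able to have a representative group", but that counts donors, not hearts with tissue.

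**The concern.** Bonferroni-Holm limits the probability of a single false positive anywhere in the family. That suits a short list of hypotheses on which a decision rests. Proteomics usually asks something else: which of many proteins are worth following up, with a known share of false leads. Applied to all measured proteins at once, the Holm rule sets a very small threshold for each protein, and with few hearts many real differences would be missed.

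The rule is stated and general. An analysis plan that used a false-discovery rate for the proteomics would depart from the one procedure that the protocol names. So this concerns how the protocol fixes the rule; it is not a complaint about detail that is properly left to an analysis plan.

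What is at stake is the yield of one secondary, exploratory analysis. Section 12 allows tissue results to be published before the primary objective is addressed, so that yield may be reported on its own.

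**Working it through.** **The plan's own figures.** None exists for the proteomics. The only calculated size, in section 7.4, is for the primary comparison. It reproduces with 90% event-free in both groups, a 10-point margin and a 1:4 ratio, if one-sided 0.025 and 80% power are assumed: (1.960 + 0.842)² × 0.9 × 0.1 × (1 + 1/4) / 0.10² = 88.3, so 89 hearts with dysfunction, and 89 / 0.20 = 445. It has no bearing on the tissue work.

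**Step 1: which rule can reject more.** Order the m p-values. At level α, Holm compares the i-th with α/(m − i + 1), and Benjamini-Hochberg compares it with iα/m. The Benjamini-Hochberg threshold is never smaller, because i(m − i + 1) − m = (i − 1)(m − i) ≥ 0. Holm stops at its first failure; Benjamini-Hochberg rejects up to the last success. So on the same p-values at the same level, Benjamini-Hochberg never rejects fewer hypotheses. This needs no assumption about the data.

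**Step 2: an illustrative base case.** From the protocol: the rule (7.3) and the 0.05 level (7.2.1, where the inequality is printed the wrong way round). Assumed: 2,000 proteins, 10% (200) truly differing by 1 SD, 20 v 20 hearts, independent two-sided two-sample t-tests.

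- The first Holm threshold is 0.05/2,000 = 0.000025. With 38 degrees of freedom the critical t is 4.80, against an expected t of about 1 × √(20/2) = 3.16. Power per protein is 8.0%. Unadjusted at 0.05 it would be 87%.
- Simulation of the full procedures (150 runs): Holm finds 8% of the true differences, about 16 of 200. Benjamini-Hochberg finds 48%, about 97 of 200, with about 5 false leads per run (4.9 / (96.9 + 4.9) = 4.8%).
- The ratio is 48/8, about 6-fold.

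**Step 3: vary every assumed input.** Percentages are shares of the true differences found. Ranges show the spread between separate simulation runs.

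| Proteins | Share differing | Hearts per group | Difference (SD) | Holm | Benjamini-Hochberg | Ratio |
|---|---|---|---|---|---|---|
| 2,000 | 10% | 20 | 1.0 | 8% | 48% | 6 |
| 5,000 | 10% | 15 | 1.0 | 1.7% | 22% | 13 |
| 5,000 | 20% | 20 | 1.0 | 4.9% | 61% | 12.5 |
| 500 | 10% | 30 | 1.0 | 38–40% | 80–81% | 2.0–2.1 |
| 2,000 | 1% | 20 | 1.0 | 8–9% | 14–15% | 1.7–1.9 |
| 2,000 | 10% | 20 | 1.5 | 50–51% | 96% | 1.9 |
| 2,000 | 10% | 50 | 1.0 | 72% | 98% | 1.4 |
| 2,000 | 10% | 100 | 0.8 | 91% | 99.7–99.8% | 1.1 |
| 50 | 10% | 20 | 1.0 | 36–37% | 47–50% | 1.3–1.4 |
| 20 | 10% | 20 | 1.0 | 50% | 56% | 1.1 |
| 2,000 | 10% | 10 | 0.8 | 0.2% | 0.4% | both negligible |

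The direction never changes, but the size changes greatly. The gain is large with many proteins, a fair share of them differing, and groups too small for Holm but large enough for Benjamini-Hochberg. It is small for a short targeted panel, large effects, large groups or few true differences. In the last row there are too few hearts for either rule to help.

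**The case against.** The strongest reply is that test families, and the error rate for an exploratory laboratory analysis, normally belong in an analysis plan or laboratory plan. Section 7 does not mention proteomics, and putting every measured protein into one Holm family is a reading of section 7.3 that its authors may not have intended. This lowers the weight of the point. It does not remove it, because the rule as worded has no exception and the tissue comparison is a listed secondary question.

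Several further points stand:

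- The wording in section 3.4 would also fit a targeted panel. For 20 to 50 proteins the two rules differ little.
- Sampling several areas of a heart permits paired comparisons within hearts. With 20 pairs, and within-heart correlations of 0.3, 0.5 and 0.7, Holm finds 11%, 24% and 61% and Benjamini-Hochberg 67%, 88% and 99%. The gap remains, but the 8% does not describe a paired analysis.
- Holm is valid and conservative, and Benjamini-Hochberg gives up family-wise control. The gain has a price.

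A reader might infer more than the documents support:

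- **That Holm leaves almost no power here and the alternative finds several times as many differences.** Neither can be stated as fact, since every input behind such figures is missing from the protocol.
- **That an empty result would be presented as proof that dysfunctional hearts are biochemically no different.** The protocol plans no such inference. The tissue comes from hearts that were not transplanted, so an empty result would say little about those that were.
- **That the planned Western blot would confirm proteomic findings.** Section 4.3.1 lists the two side by side and gives the blot no such role.

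**Conclusion.** The point holds as a cheap improvement to a secondary, exploratory analysis. Read literally, section 7.3 imposes family-wise control on the tissue proteomics, and a false-discovery-rate rule is better matched to that task. At the same level it cannot reject fewer hypotheses.

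The size of the gain is conditional. It is about 6-fold in the assumed base case, 1.1 to 2-fold for small panels, larger effects, larger groups or 1% of proteins differing, and more than 10-fold in cases such as 5,000 proteins in 15 v 15 hearts. With 10 hearts a group and 0.8 SD both rules fail. The main simulations assume independent tests and one common effect size; correlated proteins or mixed effects would change the ratios. Nothing here touches the primary comparison, the recipient outcomes or the sample size.

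**What to change.** In section 7.3, limit Bonferroni-Holm to small families of named hypotheses, and add a sentence such as: *Proteomic comparisons of donor heart tissue are exploratory and use the Benjamini-Hochberg false discovery rate at 5%, reported with effect sizes and confidence intervals.* The effect sizes and intervals let a reader tell a precise absence of difference from a lack of information, which matters if few hearts become available.

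The cost is a change of wording, with no new data and no change to any recipient analysis. The downside is that family-wise control is given up for the proteomics. On average up to about 5% of the listed proteins would be false leads (under independence 5% × 90% = 4.5% when 10% truly differ), and these need separate confirmation. If Western blot is meant to provide it, section 4.3.1 should say so.
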